### Parenting behavior

A range of studies shows that PTSD symptoms are associated with negative parenting behaviors. These include over-reactive behaviors, such as harshness, intrusiveness and overcontrol, as well as under-reactive behaviors, such as permissiveness, poor supervision, and withdrawal [56–59]. Furthermore, parents with PTSD are more likely than trauma-exposed parents without PTSD to perpetrate child maltreatment and neglect [36]. Whereas most of the literature finds PTSD symptoms to be related to more negative parenting behaviors [56], it is important to note that this association is not found in all studies (e.g., [54, 60]) and that as of yet, little is known about factors that make it more or less likely for parenting to be affected by PTSD. Furthermore, PTSD symptoms do not appear to be related to less positive parenting behaviors [56]. Thus, learning how to recognize negative parenting behaviors and replacing them with more positive alternatives may be especially important for parents with PTSD.

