### Social support

PTSD is associated with erosion of social support (defined as “actual or available social resources in times of need and groups involved that are perceived as positively supportive” [69] (p.2)). This can be harmful not only for parents with PTSD but also for their children, as lack of parental social support can also contribute to adverse child outcomes. Availability of social support resources to parents can mitigate negative effects of parental mental illness on children [70–73]. Although there is little research so far about the importance of parental social support for children of parents with PTSD specifically, its role as a buffer against intergenerational risk transmission following parental trauma exposure more generally is well-supported in the literature. For example, in mothers who had experienced childhood trauma, receiving more social support was found to diminish risk of future child maltreatment perpetration [70] and mother-child transmission of biological risk (i.e., cortisol reactivity [73]). Furthermore, social support from family members was found to buffer effects of maternal trauma exposure on child internalizing problems (at low levels of trauma exposure [71]) and externalizing problems [72]. Given these buffering effects of parental social support on adverse parenting outcomes and child risk of mental illness, we consider strengthening the parental social support network an important intervention target.

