### Study design

This study uses a two-arm randomized controlled trial (RCT) design: the intervention condition receives KopOpOuders-PTSD in addition to TAU and is compared to a control condition which only receives TAU. This design allows us to test whether the effect of KopOpOuders-PTSD in addition to TAU is superior to that of TAU only. The randomization ratio is 1:1. Block randomization (2:4:6) is used, stratified by the Arkin Mental Health Care department (Sinai Centrum or other; clients of Sinai Centrum have PTSD as their primary diagnosis, whereas clients of other departments typically do not) to ensure even distribution across conditions. Double-blind randomization is not possible, because participants and prevention professionals providing in-person sessions know automatically whether the participant is receiving the intervention. Therefore, we apply single blinding, in which the researcher overseeing the assessments and analyzing the results is blind to the condition. Randomization is done by a research assistant who is not involved in the assessments. Randomization outcomes are only accessible to this research assistant. Participants are instructed not to share their randomization outcome with the researcher overseeing their assessments, and professionals carrying out the intervention are instructed not to discuss any identifying details of intervention participants with the researcher. Unblinding is possible if needed in case of (serious) adverse events, and can be done by the primary investigator, who is not involved in assessments. To ensure parenting support is not withheld due to participation in this study, control condition participants are invited to complete the online KopOpOuders-PTSD modules after their participation and will receive information about the parenting support options at Arkin Mental Health Care.

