### Participants

#### Sample size

We assumed a medium effect size for the primary macro-level outcome (parenting behavior: Alabama Parenting Questionnaire), *d* = 0.55, based on RCTs with similar designs, interventions and populations as the current study, and with the same primary outcome [21, 82]. With a power of 0.80 and significance level of *p* = .05, the minimum *n* is 53 per condition. From previous experience with intervention studies in adults with PTSD, we expect 20–25% dropout. We therefore corrected with 25% oversampling, resulting in 53/0.75 = *n* = 71 per condition, total *N* = 142.

For the primary micro-level outcome (parenting behavior: Short Parenting Scale for EMA), power was calculated using PowerAnalysisIL [83] using our best estimation of relevant parameters. Based on existing EMA literature [84], we assume participants will respond to 70% of the 42 EMA prompts, resulting in 29 complete data points per participant. Assuming an autocorrelation between measurement occasions of *r =* 0.30 and a medium effect size, minimum sufficient power to detect intervention effects would be reached if *n =* 32 (16 per condition) agreed to take part in the EMA component of the study.

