#### Macro-level: PTSD symptoms

PTSD symptoms will be measured at pretest using the Dutch translation of the PTSD Checklist for DSM-5 (PCL-5 [107, 109]). The PCL-5 comprises 20 items describing PTSD symptoms in relation to the index trauma (e.g., ‘Becoming upset when something reminded you of the stressful experience’), which are rated for past-month frequency on a five-point Likert scale ranging from ‘Not at all’ (0) to ‘Extremely’ (4). The PCL-5 comprises four subscales corresponding to DSM-5 PTSD symptom clusters (intrusion, avoidance, negative alterations in mood and cognitions, and hyperarousal). We will use the PCL-5 total score as a moderator variable (research question 8). PCL-5 total scores range from 0 to 80. The PCL-5 has good to excellent psychometric properties, with excellent internal consistency, good test-retest reliability and good construct validity [109].

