### Analysis

Primary analyses will be conducted on the entire randomized sample (i.e., intention to treat). Extra analyses for comparison will be conducted on the per protocol/treatment completers sample. Participants in the intervention condition who have completed at least six out of eight intervention modules/sessions will be characterized as treatment completers. Participants who fail to complete the intervention, but do not choose to drop out of the study, will complete the posttest and follow-up assessments as normal. Hypothesis testing will be two-sided with an alpha level of .05. Missing data will be handled using multiple imputation (R package MICE or equivalent).

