#### Macro-level: primary and secondary outcomes

Analyses of primary (research question 1) and secondary outcomes (research questions 3–7) on the macro-level will be carried out using generalized linear mixed modeling (LMM). For ratio scale endpoints or if distributions of endpoints are skewed, robust LMM is used. Separate models are run for each endpoint. Fixed factors are condition (intervention/control), time (pretest/posttest/follow-up), and the interaction effect of condition*time. Random intercepts are fitted at the participant level. The pretest value of the endpoint is included as a control variable. In a secondary sensitivity analysis, we will also include parental gender, parental age, child age, EMA participation (yes/no), trauma type (interpersonal/non-interpersonal), child exposure to trauma (no trauma exposure/co-exposed to parental trauma/exposed to trauma separate from the parental trauma), and number of comorbid psychiatric diagnoses of the parent as covariates.

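### Pretest PCL-5 is measured before randomization but left out of both the main macro-level models and the sensitivity covariate list, so a small to modest gain in precision is passed up

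*Protocol article*

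**What the plan says.** Under 'Macro-level: primary and secondary outcomes', the protocol article gives the main models for research questions 1 and 3-7. They contain condition, time (pretest, posttest, follow-up), condition by time, a participant random intercept and the pretest value of the endpoint. The sensitivity analysis follows: "In a secondary sensitivity analysis, we will also include parental gender, parental age, child age, EMA participation (yes/no), trauma type (interpersonal/non-interpersonal", plus child trauma exposure and number of comorbid psychiatric diagnoses. That makes seven added covariates, and PTSD severity is not one of them.

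Under 'Macro-level: PTSD symptoms', the PCL-5 is taken at pretest and given one analytic role: "We will use the PCL-5 total score as a moderator variable (research question 8"). The moderation models use only the posttest measure, with condition by PCL-5 and the pretest endpoint. 'Inclusion, pretest, and randomization' places the questionnaires before allocation.

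The background ties PTSD to the outcome domains. For parenting behavior: "A range of studies shows that PTSD symptoms are associated with negative parenting behaviors". For social support: "PTSD is associated with erosion of social support". Similar statements cover perceived competence, parenting stress and child problems.

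**The concern.** PCL-5 total is a baseline variable, measured in everyone and unaffected by allocation. On the protocol's rationale it is a candidate predictor of every macro-level endpoint. The sensitivity model makes room for parental age and EMA participation, but not for the severity of the disorder that defines the population.

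Severity could predict change as well as level. All participants are in trauma therapy that continues through the study, and all macro-level outcomes are reported by the parent. The section on perceived competence says that PTSD-related cognitions color such reports.

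Two things are at stake: some precision in each between-arm contrast, and a prespecified answer if the arms happen to differ on PCL-5. Adding the covariate after seeing an imbalance would look data-driven.

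**Working it through.** **1. The plan's own figure.** 'Sample size' says: "We assumed a medium effect size for the primary macro-level outcome (parenting behavior: Alabama Parenting Questionnaire"), with d = 0.55. It continues "With a power of 0.80 and significance level of" .05, giving 53 per condition. 'Analysis' adds: "Hypothesis testing will be two-sided with an alpha level of .05". 'Study design' adds: "The randomization ratio is 1:1". A two-sample noncentral t calculation gives 53 per arm with power 0.801, and 53/0.75 = 70.7, so 71 per arm and N = 142. The figure reproduces and does not depend on PCL-5.

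**2. The quantity that matters.** The pretest endpoint is already meant to be adjusted for, so only the partial correlation r of PCL-5 with the outcome given that pretest value counts. It is not in the documents. With PCL-5 = x, pretest outcome = b and posttest outcome = y:

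r = (r_xy − r_xb·r_by) / √[(1 − r_xb²)(1 − r_by²)]

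Assume r_by = 0.5 to 0.7, and r_xy and r_xb each 0.2 to 0.4.
- Over the whole grid, |r| runs from 0 to 0.372, and r² from 0 to 0.138.
- If r_xy = r_xb, the largest value is at 0.4, 0.4 and r_by = 0.5: r = (0.4 − 0.2)/√(0.84 × 0.75) = 0.252, r² = 0.064.

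**3. What that buys.** Residual variance falls by r². Equivalent extra parents on 2 × 53 = 106 are 106·[1/(1 − r²) − 1]. Power is noncentral t at 53 per arm with effect 0.55/√(1 − r²) and one degree of freedom lost.

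| partial r | variance reduction | extra parents | power |
|---|---|---|---|
| 0 | 0% | 0 | 0.801 |
| 0.1 | 1% | 1 | 0.805 |
| 0.2 | 4% | 4 | 0.817 |
| 0.252 | 6% | 7 | 0.826 |
| 0.3 | 9% | 10 | 0.837 |
| 0.372 | 14% | 17 | 0.856 |

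This treats d = 0.55 as already scaled to the pretest-adjusted SD. If it is in raw SD units (the article does not say), pretest adjustment with r_by = 0.5 to 0.7 already takes power at 53 per arm to about 0.90-0.98. PCL-5 then adds about 1 point or less at r = 0.2, and about 1 to 2.5 points at r = 0.3.

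**4. Chance imbalance.** At 71 per arm the between-arm difference in PCL-5 has SD √(2/71) = 0.17 SD units, with a 95% range of ±0.33. It exceeds 0.2 in about 23% of randomizations and 0.3 in about 7%. With an adjusted standardized slope of 0.1 to 0.3 (assumption), an imbalance of 0.33 shifts the contrast by 0.03 to 0.10 SD, against the planned 0.55.

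**5. How the covariate must enter.** The planned model keeps pretest as a level of time. With complete (imputed) data and a random intercept, condition by time is estimated from within-person change. A PCL-5 main effect is constant within a person, so it cannot alter that contrast. A simulated complete data set confirmed this: adding PCL-5 as a main effect left the condition-by-posttest estimate unchanged, while PCL-5 by time, or modelling post-baseline rows only, did change the estimate and its standard error. The same algebra applies to the pretest endpoint entered as a main effect, so steps 2 and 3 take that adjustment to work as intended.

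**The case against.** The strongest reply is that nothing here is wrong. A randomized comparison adjusted for the pretest endpoint is valid, and that covariate is usually the strongest predictor. It also absorbs imbalance acting through baseline parenting, competence, stress or child problems. Stratification by Sinai Centrum versus other balances primary PTSD diagnosis in part. All of this stands.

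A reader might infer that the protocol itself establishes PCL-5 as prognostic for the primary outcome. It does not. The section on parenting behavior adds that the association is absent in some studies and that PTSD symptoms seem unrelated to positive parenting, which is part of the APQ total. Some of the other links compare parents with and without PTSD, whereas every participant here has it. None concerns the posttest outcome given the pretest outcome. The gain for H1 may therefore lie at the low end of the range.

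A reader might also count chance imbalance as a second harm. Averaged over randomizations it is already in the standard error. A shift of 0.3 × 0.2 = 0.06 SD is about a third of √(2/53) = 0.19.

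The moderation models do supply PCL-5-adjusted results, but at posttest only. With condition by PCL-5 in the model, the condition coefficient is the average effect only if PCL-5 is centered, which the article does not mention. They do not replace adjustment in the main models.

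**Conclusion.** The omission is real and is a stated choice: the article lists both covariate sets. It costs efficiency and some robustness, not validity. The plausible loss is 0 to 14% of residual variance, and at most about 6% if PCL-5 correlates equally with pretest and posttest outcome. On the plan's own power basis that is up to about 5.5 points (0.801 to 0.856), or about 2.5 points (0.801 to 0.826) in the equal-correlation case. It is less if d = 0.55 is in raw SD units. All of these sizes rest on assumed correlations.

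The documents do not support reading this as a biased estimate, an underpowered trial or a wrong sample size.

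**What to change.** Prespecify centered pretest PCL-5 total score as a covariate in the macro-level models for H1 and H3-H7. Enter it in one of two ways, so that it acts on the between-arm contrasts at posttest and follow-up:
- with its interaction with time, if pretest stays a level of time; or
- in a model of the posttest and follow-up rows only.

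At minimum, add it in this form to the sensitivity covariate list, which leaves the primary model untouched.

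The cost is one sentence in the analysis section and few degrees of freedom per model: three with PCL-5 by three time levels (one main effect plus two interaction terms), or one as a main effect in the post-baseline model. No new data are needed and N = 142 stands.

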#### Micro-level: primary endpoint

To test the effect of the intervention on micro-level parenting behavior (research question 2), we use a multilevel LMM in which assessments (up to 42: three per day, seven days at pretest, seven days at posttest) are nested within participants. Random intercepts are fitted at the participant level. Two dummy variables, one for measurement period (pretest/posttest) and one for condition (intervention/control) are added to the model. Differences between conditions at posttest are analyzed, while controlling for pretest scores. Because there are several assessment points per day, we control for average autocorrelation between assessment points. Finally, we control for time trends by including a variable reflecting the amount of time elapsed since inclusion.

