### Aims of this study

#### Primary objective

To test the effect of KopOpOuders-PTSD on macro- and micro-level parenting behavior by answering the following research questions:What is the effect of KopOpOuders-PTSD on macro-level parenting behavior?

H1. We hypothesize that parenting behavior at posttest will be more adaptive in the intervention condition than in the control condition. This effect is hypothesized to remain stable at follow-up.2.What is the effect of KopOpOuders-PTSD on micro-level parenting behavior?

H2. We hypothesize that micro-level parenting behavior will be significantly more adaptive at posttest in the intervention condition than in the control condition.

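### The EMA model specified for primary hypothesis H2 does not yield the posttest contrast that the same section promises, and its random-intercept structure is safe only if all parents change alike

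*Protocol article*

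**What the plan says.** H2, under Primary objective in the protocol article, is a posttest hypothesis: "micro-level parenting behavior will be significantly more adaptive at posttest in the intervention condition than in the control condition".

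The section Micro-level: primary endpoint sets out the model:

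- Rows: "assessments (up to 42: three per day, seven days at pretest, seven days at posttest) are nested within participants". Pretest and posttest reports are therefore both outcomes.
- Random part: "Random intercepts are fitted at the participant level". No random slope is named.
- Fixed terms: "Two dummy variables, one for measurement period (pretest/posttest) and one for condition (intervention/control) are added to the model".
- Target: "Differences between conditions at posttest are analyzed, while controlling for pretest scores".
- Further controls: "we control for average autocorrelation between assessment points" and "we control for time trends by including a variable reflecting the amount of time elapsed since inclusion".

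The section on the macro-level outcomes, directly before it, does name the product term for its own model: "Fixed factors are condition (intervention/control), time (pretest/posttest/follow-up), and the interaction effect of condition*time".

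**The concern.** The section states a target and a list of model terms, and the two do not fit together. With both weeks in the outcome, a posttest difference between arms needs a condition-by-period term or an equivalent constraint. None is listed. Pretest scores are also to be adjusted for although they are already outcome rows.

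At least three analyses that are not equivalent can claim to follow the text: the pooled condition coefficient, the interaction, and a posttest-only model adjusted for pretest. For a primary hypothesis that choice should not remain open until the data are in hand.

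The random part is a second matter. A random intercept alone assumes that, apart from momentary noise, every parent within an arm changes by the same amount from week 0 to week 10. If parents differ in their change, that variation is treated as independent momentary error, and the test of the interaction rejects too often.

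**Working it through.** **Inputs from the article.** Two-sided alpha 0.05; 1:1 allocation; 16 per condition as the EMA minimum; 70% of 42 prompts, given as 29 points; autocorrelation 0.30; a medium effect with no number or scale.

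**Assumptions made here.** Within-person SD 1; effect 0.5 within-person SD; EMA power 0.80 (the article gives no EMA figure); 29 points split 15 pretest and 14 posttest; ICC 0.2 to 0.4; autocorrelation handled as AR(1) residuals within each week; between-parent variance of change τ² from 0 to 0.3 in units of within-person variance.

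**Step 1: the plan's own n.** The variance of an AR(1) mean with r = 0.30 is 0.1184 for 15 points and 0.1264 for 14, sum s = 0.2448. For the difference in pre-post change between arms:

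n per arm = 2(1.96 + 0.84)²(s + τ²)/0.5²

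At τ² = 0 this is 15.4, so 16, with power 0.82. The stated 16 is reproduced, in the case where parents do not differ in change. The match depends on the scale: with 0.5 of the total SD and ICC 0.2 to 0.5, power at 16 per arm is 0.89 to 0.98.

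**Step 2: what the listed terms estimate.** With no expected difference at pretest and a posttest effect δ, a condition coefficient without interaction estimates about (0 + δ)/2. For δ = 0.5 that is 0.25. Its squared standard error at τ² = 0 is (2/16)(ICC/(1 − ICC) + s/4):

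- ICC 0.2: SE 0.197, power Φ(0.25/0.197 − 1.96) = 0.24
- ICC 0.4: SE 0.302, power 0.13

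A simulation of the additive model (300 runs, ICC 0.4, τ² = 0.1, AR(1) fitted, with time within the week as the trend term) gave a mean coefficient of 0.24 and power of 13%.

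**Step 3: interaction added, random intercept kept.** If the model ignores τ², type I error is roughly 2[1 − Φ(1.96·√(s/(s + τ²)))]. The simulation fitted both structures by REML (300 runs per setting, ICC 0.4, Monte Carlo error 1 to 2 points).

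| τ² | Formula | Simulated, 32 parents, intercept + AR(1) | Simulated, 100 parents, intercept + AR(1) | 32 parents, random period slope added |
|---|---|---|---|---|
| 0 | 0.050 | 0.043 | 0.057 | 0.033 |
| 0.1 | 0.099 | 0.083 | 0.100 | 0.053 |
| 0.2 | 0.146 | 0.110 | 0.127 | 0.073 |
| 0.3 | 0.189 | 0.153 | 0.143 | 0.057 |

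Most simulated values lie below the formula because the fitted AR(1) term absorbs part of the slope variance, but only part. With 32 parents the mean SE is 1.00, 0.90, 0.76 and 0.74 of the true SD at the four values of τ². More parents do not cure it.

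**Step 4: consequence for n.** With τ² counted, the step 1 formula gives 22, 28 and 35 per arm at τ² = 0.1, 0.2 and 0.3. Power at 16 per arm is 0.67, 0.56 and 0.48.

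**Step 5: elapsed time.** Taking EMA days as 1–7 and 71–77, the variance within a week is 4 and between weeks 35² = 1225. The correlation with the period dummy is √(1225/1229) = 0.998, and the variance inflation 1229/4 = 307. This falls on the period coefficient. In a generalised least squares check (16 per arm, 70% response, ICC 0.4), adding elapsed time multiplied the SE of the period coefficient by about 12, and that of condition by period by 1.00. With posttest slipping by up to three weeks the factors were about 8 and 1.01 to 1.02.

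**The case against.** The strongest reply is that the section does state the posttest difference as its target, immediately after the two dummies. A competent analyst would then use an interaction, or posttest rows with pretest as covariate. In the second form the condition dummy is the treatment effect and a random intercept suffices. A condensed article may also leave the random-effects detail to an analysis plan.

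Part of this stands. A reader might infer that the plan has no posttest treatment effect at all, or that it will test half the effect with power of 0.13 to 0.24. The text does not support that: those figures arise only if the pooled condition coefficient is used as the test, and the stated target points elsewhere. A reader might also infer that the standard error is certainly too small. It is not when τ² is zero, and the article gives no value for τ². Finally, the inflation factor of 307 might be read as damage to the treatment test; step 5 shows that the H2 test is practically untouched.

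What does not stand is that the stated target settles the matter. The posttest-only reading conflicts with the 42-row outcome and with the period dummy. The 42-row reading lacks the interaction and uses pretest scores as both outcome and covariate. Nor is this an omission left to a later document: the article commits to specific terms and a specific random part. Equal change for all parents is also a strong assumption in a trial whose H8 expects macro-level effects to vary with PTSD severity.

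**Conclusion.** The concern holds as an internal inconsistency in the specification of a primary analysis. The stated contrast is the right one for H2; the listed terms do not deliver it. This part needs no numerical assumption beyond randomisation making the expected pretest difference zero.

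The standard-error point is conditional. If the interaction is added to the stated random intercept, type I error with 32 parents is about 0.08 to 0.15 in simulation for τ² of 0.1 to 0.3 (0.10 to 0.19 by the simpler formula), and nominal at τ² = 0. The range of τ², the ICC and the effect scale are assumptions. The collinearity of elapsed time with period is a minor matter that does not bear on H2.

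Because a primary hypothesis is affected and the remedy is cheap, the model should be settled before any unblinded analysis.

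**What to change.** Choose one of two forms and write it out.

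1. **All 42 rows.** Fixed effects for period, condition and condition by period; a participant random intercept and a random slope for period; autocorrelated residuals within each EMA week. Test H2 on condition by period, or on the posttest difference with the pretest arm means constrained equal. Do not enter pretest scores as a covariate.
2. **Posttest rows only.** Condition as the treatment effect, the participant's own pretest EMA mean as covariate, a participant random intercept and autocorrelated residuals. Drop the period dummy.

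Replacing elapsed time by day within the EMA week is optional. It would be sensible to restate the EMA sample size over a range of τ².

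The change is one of wording and needs no new data. The price is a somewhat larger standard error than the random-intercept model would report: in the 32-parent simulation the mean SE went from 0.179 to 0.205 at τ² = 0.1, and from 0.173 to 0.181 when the slope was not needed.
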